### Patient Inclusion

Potential participants will be identified and recruited during hospitalizations in one of the participating sites. An EPR-embedded clinical rule identifies in near-real time all hospitalized patients with a BLAL in the allergy module. After checking inclusion and exclusion criteria, all eligible patients will be included in this study.

### Ethical Considerations

This clinical study was initiated after evaluation and approval by the Research Ethics Committee UZ/KU Leuven (S68439, protocol version 5, July 2, 2025), and after consultation with the ethics committees (EC) of each participating center in Belgium (Commissie voor Medische Ethiek [CME] Noorderhart [S504409]; EC St-Jozefskliniek Izegem [S504492]; CME Heilig Hart Ziekenhuis Mol [S504443]; CME AZ Herentals [S504441]; CME AZ Turnhout [S504448]; CME AZ Sint-Maria, CME RZ Tienen and CME AZ Voorkempen [approval granted; S-numbers pending]).

This study was classified as a noninterventional quality improvement project. The project does not introduce a new clinical treatment or experimental procedure but consists of systematically identifying discordances in existing electronic health records (ie, documented BLALs despite proven prior tolerance) and communicating this information to the treating physician through a decision-support process. The final clinical decision always remains with the treating physician and follows existing international and national guidelines. No additional diagnostic or monitoring procedures are imposed, and no automatic delabeling is performed by this study’s team. Therefore, this study does not mandate changes in patient management but supports standard-of-care decision-making. Under Article 2, §8 of the Belgian Law of 7 May 2004 [31], this project qualifies as a noninterventional study, as medications are prescribed according to routine clinical practice, no additional diagnostic or monitoring procedures are imposed, and epidemiological methods are used for analysis. Moreover, the risks for participants are minimal and proportionate to the anticipated benefits. However, for methodological clarity, the term “intervention” is used in this protocol but refers solely to an informational decision-support process and not to a patient-level clinical intervention.

Therefore, individual informed consent is not required. Instead, a structured patient notification and opt-out procedure is implemented in accordance with institutional policies[32].

To protect participant privacy, all study data are recorded in a secure electronic data capture system (REDCap [Research Electronic Data Capture]). Only authorized study personnel have access to identifiable data. For analysis, data are pseudonymized and stored on secure institutional servers in accordance with applicable data protection regulations, including the General Data Protection Regulation.

Participants do not receive any financial compensation or incentives for participation in this study.

### Informed Consent

Individual informed consent is not required, as this study was classified as a noninterventional quality improvement project.

Moreover, obtaining individual informed consent was considered inappropriate for several reasons: it could introduce bias by alerting physicians and/or patients of their label, potentially leading to behavioral changes compromising study validity, particularly in the control group; this study poses minimal risk, with potential disadvantages proportional to the expected benefits; the intervention targets physician prescribing behavior, not individual patients; a complete dataset is essential, excluding nonconsenting patients would limit validity and representativeness.

Instead of traditional informed consent, a structured patient notification and opt-out procedure is applied. Participants are informed through a study information letter made available via the EPR user application (Mynexuzhealth) and via the publicly accessible study webpage [33]. This study is also publicly announced through posters displayed in participating hospitals (Figure S2 in Multimedia Appendix 1). Patients are explicitly informed that they can withdraw at any time without consequences for their treatment by contacting this study’s team, as indicated in the information letter. If the dataset is not yet locked, previously collected data will be removed, and no further data will be collected. Any proposed label adjustments are actively communicated to both patients and their HCPs through the EPR (cf. Infra, communication of the AFC results, intervention group, if applicable).

These procedures were reviewed in depth and formally approved by the central ethics committee as well as by the local ethics committees of all participating sites.

### Inclusion Criteria

The inclusion criteria are hospitalized patients and BLAL (for one or more beta-lactams).

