Allocation is performed on the hospital level (participating sites) before the start of this study to prevent contamination of effect between the intervention and control phases (ie, so that physicians will not receive information through the AFC while having to use conventional means for different patients at the same time). The allocation is nonrandomized and operationally predefined based on the availability of a single trained research team responsible for on-site implementation across hospitals. Inclusion periods are sufficiently long and distributed over calendar time to account for seasonal variation. A crossover cluster-controlled design was used to reduce potential confounding related to temporal and organizational factors in clinical practice, such as variation in staffing and workload among treating physicians. Residual temporal and cluster-level confounding will be further addressed in the statistical analysis by including study period and hospital as model terms.

During separate intervention phases, hospital physicians will receive the intervention, that is, BLAL CDS. Each of the crossover periods will be 3 weeks long. However, a washout period of 3 weeks is also taken into account to allow the patient population to be sufficiently “new” before the cluster transitions to the next condition. We will use the sequences I-x-C-x, x-I-x-C, C-x-I-x, and x-C-x-I (where I=intervention, ie, use of the AFC, and C=control, ie, standard of care [SOC], no use of the AFC, and x=washout period), and each cluster will be allocated to one of these sequences (Figure 1). Information about the assigned sequence is available to all people and groups involved in the research (ie, unblinded, open study).

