### Setting

Patients will be recruited in 9 participating centers across Flanders, that is, the University Hospitals of Leuven (UZ [Universitair Ziekenhuis] Leuven), and the general hospitals of Pelt (Noorderhart Mariaziekenhuis), Mol (Heilig Hartziekenhuis), Herentals (AZ [Algemeen Ziekenhuis (general hospital)] Herentals), Turnhout (AZ Turnhout), Izegem (Sint-Jozefskliniek), Halle (AZ Sint-Maria Halle), Tienen (RZ Heilig Hart Tienen), and Malle (AZ Voorkempen). The expected recruitment period, from First Patient In to Last Patient In, is 11 months, starting March 10, 2025. The total inclusion period from First Patient In to Last Patient Out is expected to take approximately 18 months. The total period of intervention plus follow-up for every single patient depends on the LOS, that is, until 200 days after discharge from the hospital, to collect the secondary end point parameters: in-hospital mortality, 3-month posthospitalization mortality, LOS, and 3-month readmission rate. Patients who are still in the hospital when the end of the recruitment period is reached (estimated February 2026, when the needed sample size was reached) will be excluded. For comparison, in a recent retrospective study in UZ Leuven, involving 21,999 patients with pneumonia, pyelonephritis, infections associated with heart, kidney, liver, or lung transplantation, appendectomy, coronary artery bypass grafting, and total knee or hip replacement, the average LOS in UZ Leuven for patients with BLAL was 21 days (SD 39) [21].

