### Exclusion Criteria

The exclusion criteria are being aged younger than 18 years, previous enrollment in this study, patients receiving palliative care, and patients expected to be discharged within 24 hours.

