### Baseline Measurements

For each patient, baseline data will be recorded in the electronic case report form using the REDCap (cf. Infra). The collected information will encompass sociodemographic details, clinical data, and specific information on the BLALs as registered in the EPR. Sociodemographic information will include age, gender, and contact details of both the general physician and the community pharmacist. Clinical information will capture the reason for admission and, if applicable, the condition requiring antibiotic treatment, categorized according to the *ICD* (*International Classification of Diseases*) codes. Additionally, any antibiotics (Anatomical Therapeutic Chemical codes J) already administered during the current hospitalization will be documented. To assess comorbidity burden, the presence of specific conditions contributing to the Charlson Comorbidity Index will be recorded, including myocardial infarction, congestive heart failure, peripheral vascular disease, cerebrovascular disease, dementia, chronic pulmonary disease, rheumatologic disease, peptic ulcer disease, liver disease, diabetes, hemiplegia or paraplegia, renal disease, malignancy (localized or metastatic), leukemia, lymphoma, and acquired immunodeficiency syndrome. Information on BLALs will be extracted from the allergy registration module within the EPR. This will include the registration date of the BLAL, the specific drug involved (Anatomical Therapeutic Chemical code), the onset date of the allergic reaction, reported symptoms, and the source of information. Additionally, the probability of label accuracy, as indicated by the reporter, will be documented.

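### With no admission-date limit, patients already in hospital for more than 21 days can enter only a hospital's first active phase, which can bias the stay-dependent secondary outcomes

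*Protocol article*

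**What the plan says.** All places are in the Methods of the protocol article.

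- **Inclusion Criteria:** "The inclusion criteria are hospitalized patients and BLAL (for one or more beta-lactams". No limit on admission date or time already spent in hospital is stated.
- **Patient Inclusion:** "An EPR-embedded clinical rule identifies in near-real time all hospitalized patients with a BLAL in the allergy module". After the criteria are checked, "all eligible patients will be included in this study". This captures the current census, not only new admissions.
- **Baseline Measurements:** antibiotics "already administered during the current hospitalization will be documented", so enrolment partway through a stay is foreseen.
- **Exclusion Criteria:** one ground is "previous enrollment in this study".
- **Design:** active phases last 3 weeks, and "a washout period of 3 weeks is also taken into account to allow the patient population to be sufficiently" renewed before the hospital changes condition. Two of the four sequences start with intervention and two with control. Allocation is nonrandomized.
- **Setting:** in an earlier study of selected conditions, "the average LOS in UZ Leuven for patients with BLAL was 21 days (SD 39" days).
- **Statistical Analysis:** models carry phase and period terms and clustering by hospital. The patient covariates named for the adjusted primary model are age, sex and Charlson index.

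**The concern.** The washout is meant to renew the inpatient population between conditions, but it cannot do so for the first active phase, which nothing precedes. In sequences that open with a washout, nobody is enrolled during it, so the long-stay census is still there when the first active phase starts. That phase takes in long-stay patients whom the previous-enrolment exclusion then bars from all later phases.

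Length of stay, in-hospital mortality and ICU admission all depend on how long a patient stays. If one condition comes first in hospitals with long stays, this selection difference can look like an effect of the tool. For patients enrolled late in their stay, part of the stay and possibly the ICU admission also precede any action by the tool.

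**Working it through.** The plan gives no figure on this point to reproduce, so the check has three steps.

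**1. Who can enter which phase.** Take a patient who is labelled, otherwise eligible and continuously in hospital. If admitted more than 21 days before a later phase opens, that patient was present in the previous active phase, because the washout is 21 days. The patient was then already enrolled and is now excluded. Before the first active phase no such exclusion exists.

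**2. How many, and how different.** Assume a constant admission rate and stay L. Per unit admission rate, the first phase enrols E[L] patients already in hospital plus 21 new admissions. Those in for more than 21 days number E[(L−21)+].

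- Share in for more than 21 days = E[(L−21)+] / (E[L] + 21)
- Mean stay, first phase = (E[L²] + 21·E[L]) / (E[L] + 21)
- Mean stay, later phases = (E[L·min(L,21)] + 21·E[L]) / (E[L] − E[(L−21)+] + 21)

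With the Setting figures, E[L²] = 21² + 39² = 1962. The first-phase mean is (1962 + 441)/42 = 57.2 days, whatever the shape of the distribution. With a lognormal shape E[(L−21)+] = 9.63, so the share is 9.63/42 = 22.9%.

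| Stay, mean / SD (days) | Source | In >21 days, first phase | In >21 days, later | Mean stay, first | Mean stay, later |
|---|---|---|---|---|---|
| 21 / 39 | Setting (UZ Leuven) | 22.9% | 0% | 57.2 | 25.6 |
| 10 / 18 | assumed | 8.4% | 0% | 20.5 | 12.8 |
| 8 / 10 | assumed | 3.4% | 0% | 11.4 | 9.7 |
| 6 / 6 | assumed | 0.9% | 0% | 7.3 | 7.0 |

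Applying the 24-hour exclusion leaves the first-row share at 23.2%. Simulation of the 21/39 case gave 23% against 0% and a mean stay of 57 against about 26 days. Patients in hospital for up to 21 days are enrolled when any phase opens, so later phases resemble one another.

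**3. What reaches the treatment contrast.** The first-phase excess in mean stay is 57.2 − 25.6 = 31.6 days at a UZ Leuven-like site and 11.4 − 9.7 = 1.7 days at an 8/10 site.

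- If all hospitals start together and share the same shift, phase order coincides with period. The period term then removes it, and the computed bias is 0.
- With unequal shifts, suppose the long-stay site supplies half the patients of one order group (assumption) and there is one intervention/control pass. The error with no effect of the tool is (0.5×31.6 + 0.5×1.7 − 1.7)/2 = 7.5 days.
- One pass takes 4 × 3 = 12 weeks and recruitment was planned for 11 months, about 48 weeks, so about four passes fit. Only one of each hospital's four pairs of phases is then affected: 7.5/4 = 1.9 days.

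A refit with hospital, period and phase terms used shifts of 31 days at one site and 1.5 at eight, sequences assigned arbitrarily, and the academic site supplying 30–50% of all patients (assumed). With a common start the mean absolute error was 6.2–7.8 days for one pass and 1.5–2.0 days for four. With three hospitals joining after the others the averages were similar (6.3–7.4 and 1.6–1.8), although single unfavourable arrangements went higher, to 3.7 days with four passes. The sign depends on which condition the long-stay site runs first.

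**The case against.** Much can be said on the other side.

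- **Reach.** A reader might infer that intervention and control phases hold different populations throughout. The rules do not imply that. Only the first active phase differs, and later intervention and control phases are alike.
- **Size.** A reader might take an error of about 7 days as the expected one. It needs a single pass and a heavily weighted academic site. The design figure is not shown, so the number of passes is not known, but the recruitment period points to several.
- **Input.** The 21-day mean comes from one academic centre and selected conditions that include transplantation. Eight of the nine sites are regional, and with short stays the imbalance is small.
- **Design safeguards.** Both orders are used, and the period term removes a common shift completely.
- **Primary endpoint.** It is a proportion of applicable windows. More windows per patient do not by themselves move a proportion.
- **Left to the analysis plan.** The time origin of the outcomes and further covariates may be settled there, and the Discussion already concedes residual confounding.

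These points limit the weight of the concern but do not remove it. The selection follows from stated eligibility rules, the named covariates do not include time since admission, and the period term does not correct shifts that differ between hospitals.

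**Conclusion.** The point holds in a limited form. Under the stated rules, patients in hospital for more than 21 days enter only a hospital's first active phase. Their share there runs from about 1% to 23%, depending on stay length and on an assumed lognormal shape.

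Stays differ between hospitals, order is nonrandomized and three hospitals join later, so some bias can remain in length of stay, in-hospital mortality and ICU admission. Only length of stay has been sized: about 1–2 days on average if the sequence repeats about four times, and about 6–8 days only under a single pass with a large academic share. Those figures assume constant admissions, ignore readmissions, and rest on assumed regional stays.

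A reader might also infer that the primary result is compromised. Nothing in the document or in these calculations shows that. This is a cheap improvement to make, not a flaw that invalidates the trial.

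**What to change.** Before database lock, prespecify one admission look-back for every phase: the analysis set keeps patients admitted no more than 21 days before the phase in which they were enrolled opened. The EPR admission date is enough to apply it to patients already enrolled.

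- Use this set for length of stay, ICU admission and in-hospital mortality, and as a sensitivity analysis for the primary endpoint.
- Count the three stay-dependent outcomes from inclusion.
- Add days from admission to inclusion as a covariate.
- Report the uncapped set alongside.

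The cost is one date filter, one covariate and a short amendment. The filter removes about 1–4% of first-phase patients where stays are short, up to about 23% where they resemble UZ Leuven's, and none from later phases. Fixing it before results are seen keeps it from being post hoc.

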### Exclusion Criteria

The exclusion criteria are being aged younger than 18 years, previous enrollment in this study, patients receiving palliative care, and patients expected to be discharged within 24 hours.

### Baseline Measurements

For each patient, baseline data will be recorded in the electronic case report form using the REDCap (cf. Infra). The collected information will encompass sociodemographic details, clinical data, and specific information on the BLALs as registered in the EPR. Sociodemographic information will include age, gender, and contact details of both the general physician and the community pharmacist. Clinical information will capture the reason for admission and, if applicable, the condition requiring antibiotic treatment, categorized according to the *ICD* (*International Classification of Diseases*) codes. Additionally, any antibiotics (Anatomical Therapeutic Chemical codes J) already administered during the current hospitalization will be documented. To assess comorbidity burden, the presence of specific conditions contributing to the Charlson Comorbidity Index will be recorded, including myocardial infarction, congestive heart failure, peripheral vascular disease, cerebrovascular disease, dementia, chronic pulmonary disease, rheumatologic disease, peptic ulcer disease, liver disease, diabetes, hemiplegia or paraplegia, renal disease, malignancy (localized or metastatic), leukemia, lymphoma, and acquired immunodeficiency syndrome. Information on BLALs will be extracted from the allergy registration module within the EPR. This will include the registration date of the BLAL, the specific drug involved (Anatomical Therapeutic Chemical code), the onset date of the allergic reaction, reported symptoms, and the source of information. Additionally, the probability of label accuracy, as indicated by the reporter, will be documented.

### AFC CDS Tool (Intervention Group)

A clinical rule embedded in the EPR checks in near-time for re-exposure to the culprit antibiotic or class member, from the date of BLAL registration to the date of patient inclusion (the AFC). The AFC is incorporated into the hospital information system as an “if-then” algorithm, using real-time structured data available in the EPR. The AFC incorporates information from the electronic prescribing module in the EPR and uses an integrated natural language processing tool to identify re-exposures since the introduction of the BLAL in the various EPR records. Additionally, it lists data on coadministration of antihistamines, glucocorticoids, or epinephrine during the re-exposure period, up to 24 hours after the last antibiotic dose. These medications are considered proxies for possible allergic reactions and help inform the subsequent review process. The results of the screening, that is, the clinical rule alerts, are compiled on a structured worklist in the hospital information system for secondary review by a specified trained person, that is, a member of the study team in the current study, before alerting the treating physician [24]. Validated flowcharts are used to support the review, ensuring a standardized and systematic approach. Schematic algorithms are used to guide the actual delabeling or refinement advice based on the allergy label, subsequent exposure, and consequences linked to this exposure (Figure S3 in Multimedia Appendix 1).

Consulting primary care data could not yet be automated due to the lack of interoperability between different EPRs. In order to retain a focus on the impact of the AFC alone, we did not systematically obtain information from the primary care HCP (physician and/or pharmacist) on beta-lactam re-exposure. In our pilot study [30], this step provided only a minor contribution.

Based on the collected information, BLALs are allocated to 3 groups: to delabel, to refine, or to leave as such. An incorrect BLAL is assigned when patients reported a clearly nonallergic adverse drug reaction, when a negative rechallenge or uneventful re-exposure was identified since registration of the BLAL; a correct BLAL is assigned when an allergic reaction was observed in the hospital or when positive skin and/or provocation testing was found; and an undetermined BLAL is assigned when there is no proof of correctness or incorrectness of the BLAL. Allocation is performed by a member of this study’s team, and if needed, discussed and validated with the principal investigator.

